| 0.15                 | 3.44 | 0.75                   | 2.58    | 2.97  | 351   | 0.42     | 843 | 0.15       | 970             |
| 0.2                         | 3.44        | 0.75                          | 2.58           | 3.10         | 202          | 0.42            | 485        | 0.15              | 558                    |

\*Adjusted for estimated bed net use and loss to follow-up

**5.2 Procedures***Recruitment, Randomization Process and Blinding*

Subjects will be recruited from villages in the Kintampo Health Research Centre (KHRC) study area once permission has been obtained from the village assemblies and elders, as well as the parent or guardian of the eligible child. Field researchers, employed by the KHRC, will visit individual households/compounds and interview parents or caregivers regarding the inclusion criteria. Once consent has been obtained and documented via signature or thumbprint, eligible children (one per household/compound) will be enrolled and randomized, using a computer-generated model, to either the iron (Fe) or placebo (P) group.

Sachets containing the powdered minerals with and without iron will look and taste identical with the exception that each package will be marked with an 'A' or 'B' denoting packages with or without iron. The study team and caretakers of children will be blinded to the 'A' or 'B' designation. Only the manufacturer of the powdered fortificant (in Ghana) and a research pharmacist each in Toronto and Kintampo will hold the key to the randomization and 'sachet' code lists. The key will be revealed to the 'Data and Safety Monitoring Committee (DSMC)' at the end of the first phase if a significant difference in outcomes is observed, and to the researchers after the database is closed and statistical analyses completed.

*Supply and content of the powdered mineral and vitamin fortificant.*

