##### Primary analysis

The primary outcome, incidence of malaria, will be compared between the two groups using Poisson regression. A 95% confidence interval for the ratio between the incidence in the iron group and the incidence in the placebo group will be calculated. The upper boundary of this confidence interval will be compared to the 10% tolerance limit. If it is lower, then non-inferiority can be concluded.

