##### Secondary analysis

Univariate Poisson regression with the same outcome will be used to evaluate associations with other variables: iron status at baseline, breast-feeding, age, gender and use of bed-net. These will then be introduced and re-evaluated in a multiple Poisson regression model, which will allow for adjusted group comparisons. Most importantly, by including the baseline iron status variable and the interaction with the main group variable, we can focus on the iron sufficient children that are receiving iron supplements and compare them against the others. The Poisson models will be validated by checking the model fit and for over-dispersion. Adjustments or transformations will be used if necessary.

The number of hospital admissions will be analyzed in a similar fashion, using Poisson regression. The parasite count outcome will be compared between the two groups, using a t-test. Univariate associations with other factors will be verified here as well, using t-tests, correlation coefficients and univariate regression.

Ultimately a multiple regression model will be developed, again for the purpose of adjusted comparisons between groups.

The normality of the data will be verified and, in the case of any departures, a log-transformation will be used and the data reanalyzed. If the log-transformation fails to achieve normality, a nonparametric alternative will be used instead. All statistical analyses will be carried out using SAS 9.1. The Analysis will be carried out on an intention-to-treat basis including all randomized children.

Upon the completion of the first intervention phase, an interim analysis will be performed by a Data and Safety Monitoring Committee (DSMC) as described above (primary analysis). The study will be stopped if the incidence of malaria is higher in one group.

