## **5.8 Potential Difficulties and Limitations**

a) Blinding: Although research staff will be blinded to the intervention, the stools of children receiving the iron containing fortificant will likely be darker (blackier) than those receiving the placebo. The applicants are unable to control for this likelihood.

b) If after the first phase (the dry season) there is more clinical malaria or more severe malaria or health complications in the group receiving the iron-containing fortificant, the DSMC may recommend terminating the study before the second phase begins.

c) It will not be possible to compare the results of the proposed current study to many of the results from the Pemba study. In Pemba, the primary outcome was mortality, which necessitated a sample size of more than 30,000 subjects. Also, in the current protocol, folic acid will not be included in the powdered mineral and vitamin supplement. Based on the estimated dietary folic acid intake of older infants and children in West Africa, folic acid deficiency should not be a problem (fruit is plentiful and inexpensive). Lastly, in the current protocol all children will receive and be encouraged to use bed-nets. This was not the case in the Pemba study.

d) Although studies in adults have suggested that elevations in TfR (82) or in ZnPP (75) can be definitive indicators of iron deficiency, there is large overlap in the distributions of these indicators in children with iron deficiency anemia as well as those with normal iron status. This overlap may be explained by a greater variability in the erythroid mass in children than in adults (83) together with the many variables affecting children in developing countries that influence TfR and ZnPP independent of iron status. Because of this overlap, the sensitivity and specificity of TfR and ZnPP in identifying iron deficiency and IDA may not be as high as we would prefer regardless of the diagnostic cutoffs chosen. Despite this limitation, all three biomarkers of iron status, ferritin, TfR and ZnPP, will be statistically evaluated individually and in groupings since this measure is very important in the context of the current study.

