| Data management setup                                                            | Ghana         | 12               |          |          |          |          |          |          |          |          |          |          |          |          |          |          |          |          |          |
| Clearing of supplies                                                             | Ghana         | 12               |          |          |          |          |          |          |          |          |          |          |          |          |          |          |          |          |          |
| Recruitment of subjects for first cohort                                         | Ghana         | 8                |          |          |          |          |          |          |          |          |          |          |          |          |          |          |          |          |          |
| Complete Phase 1                                                          | Ghana         | 22               |          |          |          |          |          |          |          |          |          |          |          |          |          |          |          |          |          |
| Biochemical analyses                                                             | Ghana         | 8                |          |          |          |          |          |          |          |          |          |          |          |          |          |          |          |          |          |
| Cleaning and compiling data (primary outcome) for DSMC assessment                | Toronto/Ghana | 2                |          |          |          |          |          |          |          |          |          |          |          |          |          |          |          |          |          |
| DSMC assessment                                                                  | Toronto/Ghana | 2                |          |          |          |          |          |          |          |          |          |          |          |          |          |          |          |          |          |
| Preparation Phase 2                                                              | Toronto/Ghana | 2                |          |          |          |          |          |          |          |          |          |          |          |          |          |          |          |          |          |

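### The Phase I stopping rule in section 5.5 has no significance level and no direction, and it conflicts with section 5.8(b)

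*Protocol*

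**What the plan says.** The last paragraph of section 5.5 (under Secondary analysis) has the monitoring committee repeat the primary analysis once the first phase is complete, and then adds: "The study will be stopped if the incidence of malaria is higher in one group".

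The primary analysis fits a Poisson model. "A 95% confidence interval for the ratio between the incidence in the iron group and the incidence in the placebo group will be calculated", and "The upper boundary of this confidence interval will be compared to the 10% tolerance limit". If the upper limit is below the tolerance, non-inferiority is concluded.

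Three other places bear on the same decision:

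- Section 5.8(b) considers the case of "more clinical malaria or more severe malaria or health complications in the group receiving the iron-containing fortificant" after the dry season, in which "the DSMC may recommend terminating the study before the second phase begins".
- Section 5.2 (Recruitment, Randomization Process and Blinding) has the treatment code revealed to the committee "at the end of the first phase if a significant difference in outcomes is observed".
- The timetable in section 5.9 has a row "Cleaning and compiling data (primary outcome) for DSMC assessment". Secondary outcomes appear only in a later row, compiled after both phases.

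**The concern.** The sentence in 5.5 is a firm rule rather than a placeholder, and it cannot be applied as it stands. It does not say how much higher, at what level of evidence, or in which arm. The analysis it refers to answers a different question: an upper limit compared with 1.10 can show non-inferiority, but it does not say when one arm's incidence counts as higher.

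The rule also disagrees with 5.8(b) on force (mandatory against advisory), on direction (either arm against an iron excess) and on outcomes (malaria incidence against incidence, severity and complications).

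It decides whether the second cohort of 1,940 children, half of the planned 3,880, is enrolled at all. That cohort covers the season of higher transmission. Section 5.1 says an effect may be absent in the dry season and present in the wet, and treats that contrast as a possible basis for a season-specific programme.

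**Working it through.** **Inputs.** Table 1: unexposed rate 3.44 × 0.75 = 2.58 episodes per child-year; 15% increase, so 2.58 × 1.15 = 2.967; 351 person-years, applied per group as the table's columns imply; 80% power; 5% type I error, adjusted for testing twice.

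**Reproducing Table 1.** Person-years per group = (z_α + z_β)² (r0 + r1)/(r1 − r0)², where (r0 + r1)/(r1 − r0)² = 5.547/0.387² = 37.04.

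| Level | (z_α + z_β)² | Person-years |
|---|---|---|
| One-sided 5% | (1.645 + 0.842)² = 6.18 | 229 |
| Two-sided 5% | (1.960 + 0.842)² = 7.85 | 291 |
| Two-sided 2.5% | (2.241 + 0.842)² = 9.50 | 352 |

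The protocol states 351. At two-sided 2.5% the other rows also match: 3021, 774 and 203 against the stated 3017, 772 and 202. Then 351/(5/12) = 842.4, rounded up to 843, and 843 × 1.15 ≈ 970. So the sizing used 5% divided over two tests, while the analysis text uses a 95% interval.

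**Literal reading, no true effect.** Expected episodes per group are 351 × 2.58 = 905.6. The rule fails to trigger only on an exact tie. For two Poisson counts with equal mean μ, P(tie) ≈ 1/√(4πμ) = 1/√(4π × 905.6) = 0.0094 (the exact Skellam value is also 0.0094). One arm is therefore higher with probability 0.991, or 0.495 each way.

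The protocol gives no dry-season rate, so lower rates are assumed:

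| Rate | Expected episodes per group | P(one arm higher) |
|---|---|---|
| 2.58 | 905.6 | 99.1% |
| 1.29 (half) | 452.8 | 98.7% |
| 0.645 (quarter) | 226.4 | 98.1% |

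With unequal person-time, exact ties almost vanish and the figure approaches 100%.

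**Significance reading.** Wald test on the log rate ratio, Poisson counts, 905.6 expected episodes in the placebo group, 400,000 simulated trials:

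| True rate ratio | Event | Two-sided 5% | Two-sided 2.5% |
|---|---|---|---|
| 1.00 | Stop, either direction | 4.9% | 2.5% |
| 1.00 | Stop, iron higher | 2.5% | 1.3% |
| 1.15 | Stop, iron higher | 87% | 80% |

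**Lower dry-season rate.** At half the rate, SE = √(1/452.8 + 1/520.7) = 0.0643 and ln(1.15)/SE = 2.175. The chance of stopping under a true 15% increase is then Φ(2.175 − 1.960) = 58.5% at the 5% level and Φ(2.175 − 2.241) = 47.4% at 2.5%.

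**A result favouring iron.** Suppose, purely for illustration, that iron lowers incidence by 10%. At the planned rate, SE = √(1/905.6 + 1/815.0) = 0.0483 and |ln(0.90)|/SE = 2.182. A two-directional rule would stop because placebo is higher with probability Φ(2.182 − 1.960) = 59% at 5% and Φ(2.182 − 2.241) = 48% at 2.5%.

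**The case against.** The strongest reply is that nobody would apply the sentence literally, and much of this stands. The interim is tied to a Poisson model with a confidence interval. The sample size is adjusted for testing the hypothesis twice, which a bare comparison of two counts would not need. Section 5.1 expects the wet-season phase to follow a dry season in which nothing is detected. Section 5.2 speaks of a significant difference. A reader might infer from the 99% figure that the wet-season cohort would almost never run. The protocol does not support that inference: 99% describes the wording, not the committee's likely conduct.

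A reader might also take 5.2 as a third, competing stopping rule. It is not one. It governs when the code is revealed, and it favours the significance reading. Nor does 5.8(b) say that only an iron excess can stop the trial; it describes one scenario. Section 8.1c names a malaria risk for anemic children in the control group, so a symmetric rule has some basis.

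The timetable point is modest. The timetable is tentative, one row label names only the primary outcome, and the text below it has the committee reviewing outcomes in the plural. Adverse events are also reviewed weekly under section 8.5.

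Finally, section 8.5 promises a detailed monitoring plan before accrual, and numerical boundaries may sit there or in the SAP. A missing boundary alone would therefore not be a finding. But the protocol does state a rule. That rule is unusable as worded and conflicts with 5.8(b), and a later document would have to contradict it to repair it.

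**Conclusion.** The point holds as a badly stated rule and an internal conflict. Section 5.5 orders the study stopped on a condition with no level and no direction, and the cross-referenced primary analysis supplies neither. Literally, the condition is met in 98 to 99% of null trials over the rates assumed. On the more plausible significance reading, false stops are about 2.5 to 5%, depending on a level the protocol leaves open between its 95% interval and the 2.5% implied by Table 1.

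The conflict with 5.8(b) remains on either reading, as does the possibility that a dry-season result favouring iron ends the trial before the wet season is studied.

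The figures assume Poisson counts and the planned 351 person-years per group. Over-dispersion, which section 5.5 itself plans to check, would raise the false-stop rates if standard errors were left uncorrected. The 2.5% level is inferred from reproducing Table 1; it is not stated in the protocol.

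**What to change.** Replace the stopping sentence in 5.5 with one statistical criterion for the interim comparison. It should state the confidence level and the direction, use standard errors corrected for over-dispersion, and be consistent with Table 1's adjustment for two tests. One example is that the lower limit of the two-sided 97.5% confidence interval for the iron:placebo rate ratio lies above 1.

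Reconcile 5.5 with 5.8(b) on mandatory against advisory and on either arm against the iron arm. Keep the committee's own safety judgement alongside the statistical criterion, and align the unblinding wording in 5.2.

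Change the timetable row so that severe malaria, admissions and deaths by arm reach the committee with the primary outcome. This matches 5.8(b) and the text under the timetable.

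The cost is protocol wording and a somewhat larger interim data cut, with no extra children. State the statistical price openly: at the planned rate, the 2.5% level stops for a true 15% increase about 80% of the time against 87% at 5%. At an assumed half rate in the dry season, the figures are about 47% against 58.5%.

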## **5.6 Data Interpretation**

Findings from the proposed research will provide evidence regarding the safety and efficacy of providing daily iron supplementation (12.5 mg/day), in the form of a micronutrient powder that is added to complementary foods, during the dry and wet season in a malaria endemic area.

## **5.7 Data Sharing Plan**

Findings from the proposed research will be shared according to the applicable NIH policy for foreign institutions.

## **5.8 Potential Difficulties and Limitations**

a) Blinding: Although research staff will be blinded to the intervention, the stools of children receiving the iron containing fortificant will likely be darker (blackier) than those receiving the placebo. The applicants are unable to control for this likelihood.

b) If after the first phase (the dry season) there is more clinical malaria or more severe malaria or health complications in the group receiving the iron-containing fortificant, the DSMC may recommend terminating the study before the second phase begins.

c) It will not be possible to compare the results of the proposed current study to many of the results from the Pemba study. In Pemba, the primary outcome was mortality, which necessitated a sample size of more than 30,000 subjects. Also, in the current protocol, folic acid will not be included in the powdered mineral and vitamin supplement. Based on the estimated dietary folic acid intake of older infants and children in West Africa, folic acid deficiency should not be a problem (fruit is plentiful and inexpensive). Lastly, in the current protocol all children will receive and be encouraged to use bed-nets. This was not the case in the Pemba study.

d) Although studies in adults have suggested that elevations in TfR (82) or in ZnPP (75) can be definitive indicators of iron deficiency, there is large overlap in the distributions of these indicators in children with iron deficiency anemia as well as those with normal iron status. This overlap may be explained by a greater variability in the erythroid mass in children than in adults (83) together with the many variables affecting children in developing countries that influence TfR and ZnPP independent of iron status. Because of this overlap, the sensitivity and specificity of TfR and ZnPP in identifying iron deficiency and IDA may not be as high as we would prefer regardless of the diagnostic cutoffs chosen. Despite this limitation, all three biomarkers of iron status, ferritin, TfR and ZnPP, will be statistically evaluated individually and in groupings since this measure is very important in the context of the current study.

## **5.9 Tentative Project Timetable**

| Tasks                                                                            | Location      | Duration (weeks) | Jun 2009 | Sep 2009 | Oct 2009 | Nov 2009 | Dec 2009 | Mar 2010 | Apr 2010 | May 2010 | Jun 2010 | Oct 2010 | Nov 2010 | Dec 2010 | Jan 2011 | Feb 2011 | Mar 2011 | Apr 2011 | May 2011 |
|----------------------------------------------------------------------------------|---------------|------------------|----------|----------|----------|----------|----------|----------|----------|----------|----------|----------|----------|----------|----------|----------|----------|----------|----------|
| Ethics approval                                                                  | Toronto/Ghana | 12               |          |          |          |          |          |          |          |          |          |          |          |          |          |          |          |          |          |
| Procurement of supplies                                                          | Toronto/Ghana | 12               |          |          |          |          |          |          |          |          |          |          |          |          |          |          |          |          |          |
| Data management setup                                                            | Toronto/Ghana | 12               |          |          |          |          |          |          |          |          |          |          |          |          |          |          |          |          |          |
| Shipping                                                                         | Toronto/Ghana | 12               |          |          |          |          |          |          |          |          |          |          |          |          |          |          |          |          |          |
| Development of training materials                                                | Ghana         | 12               |          |          |          |          |          |          |          |          |          |          |          |          |          |          |          |          |          |
| Training of staff                                                                | Ghana         | 12               |          |          |          |          |          |          |          |          |          |          |          |          |          |          |          |          |          |
| Data management setup                                                            | Ghana         | 12               |          |          |          |          |          |          |          |          |          |          |          |          |          |          |          |          |          |
| Clearing of supplies                                                             | Ghana         | 12               |          |          |          |          |          |          |          |          |          |          |          |          |          |          |          |          |          |
| Recruitment of subjects for first cohort                                         | Ghana         | 8                |          |          |          |          |          |          |          |          |          |          |          |          |          |          |          |          |          |
| Complete Phase 1                                                          | Ghana         | 22               |          |          |          |          |          |          |          |          |          |          |          |          |          |          |          |          |          |
| Biochemical analyses                                                             | Ghana         | 8                |          |          |          |          |          |          |          |          |          |          |          |          |          |          |          |          |          |
| Cleaning and compiling data (primary outcome) for DSMC assessment                | Toronto/Ghana | 2                |          |          |          |          |          |          |          |          |          |          |          |          |          |          |          |          |          |
| DSMC assessment                                                                  | Toronto/Ghana | 2                |          |          |          |          |          |          |          |          |          |          |          |          |          |          |          |          |          |
| Preparation Phase 2                                                              | Toronto/Ghana | 2                |          |          |          |          |          |          |          |          |          |          |          |          |          |          |          |          |          |
| Recruitment of subjects for second cohort                                        | Ghana         | 8                |          |          |          |          |          |          |          |          |          |          |          |          |          |          |          |          |          |
| Complete Phase 2                                                          | Ghana         | 22               |          |          |          |          |          |          |          |          |          |          |          |          |          |          |          |          |          |
| Biochemical analyses                                                             | Ghana         | 8                |          |          |          |          |          |          |          |          |          |          |          |          |          |          |          |          |          |
| Cleaning and compiling data (primary and secondary outcomes) from Phases 1 and 2 | Ghana         | 8                |          |          |          |          |          |          |          |          |          |          |          |          |          |          |          |          |          |
| Data analysis                                                                    | Toronto/Ghana | 4                |          |          |          |          |          |          |          |          |          |          |          |          |          |          |          |          |          |
| Manuscript writing and submission                                                | Toronto/Ghana | 8                |          |          |          |          |          |          |          |          |          |          |          |          |          |          |          |          |          |

The timing of this study is complicated by the need to enroll and study subjects during two distinct seasons, the dry season (December to April) and the wet season (June to October). Because of the need to have the 'data and safety monitoring committee (DSMC)' review the outcomes between seasons, we will ensure that the data sets are complete and 'clean' by mid May, leaving the DSMC two weeks to complete their analysis. Note that some periods overlap. For example, the biochemical analysis will take place during and at the end of the trial.

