## 5. RESEARCH DESIGN AND METHODS

### 5.1 Design Conceptual or Clinical Framework

#### *Study Design*

The proposed study is a community-based blinded randomized controlled trial with 2 study arms that will be conducted in two phases:

- Phase I will take place during the dry season (December to April), when malaria transmission rates are lower. Eligible subjects (one per household) will be individually randomized to receive a daily dose of either a powdered vitamin/mineral fortificant containing 12.5 mg of iron (plus ascorbic acid, vitamin A and zinc), or a placebo (containing all micronutrients excluding iron), added to complementary foods, for 5 months.
- Phase II will take place during the wet season (June to October), when malaria transmission rates are higher. Eligible subjects, who did not participate in Phase I, will be individually randomized to one of the two study arms as described above and followed for 5 months.

A dual phase design, with two unique cohorts, was chosen so that preliminary results (at the end of phase 1) could be assessed by an independent Data Safety and Monitoring Committee. It is possible that during the dry season no impact of iron will be detected, while during the wet season, an impact will be observed. With this possible outcome, it is potentially feasible to translate this knowledge into a Ministry of Health Program to only provide iron supplementation (fortification) during the dry months of the year (December to April).

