### **8.5 Data and Safety Monitoring Plan**

- General description of a monitoring plan that will establish as the overall framework for data and safety monitoring. Describe entity that will be responsible for monitoring and the process by which Adverse Events will be reported to the Institutional Review Board, the funding I/C, the NIH Office of Biotechnology Activities (OBA), and the Food and Drug Administration (FDA) in accordance with Investigational New Drug (IND) or Investigational Device Exemption (IDE) regulations.
  - i. Field workers will describe any possible adverse events to the field supervisors. At weekly meetings with the study site coordinator, potential adverse events will be reviewed. A written summary of this weekly meeting will be shared with the co-investigator who will decide if the information should be shared with the PI. Any adverse events reported to the PI will be reported to the IRBs in Ghana and Canada.
- Options for monitoring trials include, but not limited to: PD/PI (required); Institutional Review Board (required); Independent individual/safety officer; Designated medical monitor; Internal Committee or Board with explicit guidelines; Data and Safety Monitoring Board (required by NIH for multi-site clinical trials involving interventions that entail potential risk to participants, and generally for Phase III clinical trials)
  - i. A detailed Data and Safety Monitoring Plan will be submitted to IRBs in both Toronto and Ghana and (subsequently) the funding IC for approval prior to the accrual of human subjects.

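### The Phase I DSMC data package covers clinical malaria only, although severity and complications are also termination grounds, and 8.5 puts a discretionary step between serious adverse events and the PI and IRBs

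*Protocol*

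**What the plan says.** **Grounds for termination.** Section 5.8(b) says the DSMC may recommend ending the study before the second phase if there is "more clinical malaria or more severe malaria or health complications in the group receiving the iron-containing fortificant".

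**Content of the interim.** Section 5.5 says "an interim analysis will be performed by a Data and Safety Monitoring Committee (DSMC) as described above (primary analysis"), that is, Poisson regression of malaria incidence. The only ground it gives is "The study will be stopped if the incidence of malaria is higher in one group".

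**Data prepared.** The timetable row before the DSMC assessment in 5.9 is "Cleaning and compiling data (primary outcome) for DSMC assessment" (2 weeks). The only row that names secondary outcomes comes after Phase 2: "Cleaning and compiling data (primary and secondary outcomes) from Phases 1 and 2" (8 weeks).

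**Adverse events.** Under 8.5, field workers tell supervisors, events are reviewed at a weekly meeting, and a written summary is "shared with the co-investigator who will decide if the information should be shared with the PI". Events that reach the PI go to the IRBs in Ghana and Canada. The same section promises a detailed monitoring plan before accrual.

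**The concern.** A committee can act on a termination ground only if it is given the data for it. Section 5.8(b) names three grounds, while the file and analysis specified in 5.9 and 5.5 serve the first. Section 3.1 reports that the harm in the Pemba trial was increased hospitalization and mortality, and that the iron arms there were discontinued on its monitoring board's advice. Followed as written, this DSMC would decide whether the higher-transmission phase should start without a cleaned file of that class of event. The individual-event route in 8.5 does not clearly make up for this, because it has a discretionary step with no exception for deaths or admissions and does not mention the DSMC.

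**Working it through.** **1. How many tests the plan budgets for.** The inputs are in 5.1 (Sample Size, Table 1): baseline 3.44 per child-year, bed-net factor 0.75, 15% increase, 80% power, 5% type I error. The rates are r1 = 3.44 × 0.75 = 2.58 and r2 = 1.15 × 2.58 = 2.967. Person-years per arm = (z_alpha + z_power)² × (r1 + r2) / (r2 − r1)².

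- Two-sided 0.05: (1.960 + 0.842)² × 5.547 / 0.387² = 290.7, which does not match the stated 351.
- Two-sided 0.025 (0.05 split over two tests): (2.241 + 0.842)² × 5.547 / 0.387² = 352.0, which matches 351 to rounding.

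Table 1 therefore assumes one interim and one final test, as the text says. This counts tests of the primary hypothesis only. It cannot show whether safety-only reviews are planned.

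**2. The 5.8(b) grounds set against the outcomes.** Section 2 measures severity by parasite counts and hospital admissions, and names death, cerebral malaria, pneumonia, dehydration and diarrhea as complications. Section 5.1 makes all of these secondary outcomes:

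| Outcome (number in 5.1) | Source of data | Covered by a primary-outcome file? |
|---|---|---|
| Severity by parasitemia (ii) | Same smear as the primary outcome | Obtainable, though not listed |
| Cerebral malaria (iii) | Coma score plus count (5.3) | Not stated |
| Hospitalization, any cause (iv) | Facility tracking (5.2(c)) | Not stated |
| Death (v) | Cause-specific classification (5.3) | Not stated |
| Pneumonia (vi) | Clinical signs and X-ray (5.3) | Not stated |
| Diarrhea and dehydration (vii) | Clinical signs (5.3) | Not stated |

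So five of the six outcomes that bear on severity or complications have no stated place in the file. Severe malaria disease in 5.3 also rests on signs at presentation or during admission, which a smear does not supply.

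**3. Order of tasks in 5.9.** The order is Phase 1, cleaning of the primary outcome (2 weeks), DSMC assessment (2 weeks), preparation, recruitment and completion of Phase 2, then cleaning of primary and secondary outcomes (8 weeks). The same table uses two different labels for the two cleaning tasks.

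**4. The route in 8.5.** Field worker → supervisor → weekly meeting → co-investigator → (if so decided) PI → IRBs. Seriousness does not alter the route, and the DSMC is not on it.

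**5. Size.** The decision concerns the start of a cohort of 1,940 children (970 per group). The protocol gives no death or admission rate, so expected numbers of unseen events cannot be derived from it.

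**The case against.** The best defense is that the text is loose and does not exclude these data. The paragraph under the 5.9 timetable has the DSMC reviewing outcomes, in the plural and without restriction, on complete data sets. Section 5.2 likewise ties release of the key to a difference in outcomes. Section 5.4 requires field data to be entered by the end of the next day and all outcomes to be double-entered, so secondary data should be on file by May. The post-Phase 2 row relists the Phase 1 primary outcome, so it probably describes the pooled final file. The timetable is labeled tentative. All of this stands, and it means the protocol contradicts itself; a general word does not override a specific row and a specific definition of the interim analysis. It is also right that parasite-count severity is within reach.

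A reader might infer more: that the DSMC is barred from secondary data, that adverse events can never reach it, that events found through identity cards fall outside the 8.5 route, or that the wet season has no review. The documents do not support these readings. Section 8.5 covers any possible adverse event and excludes no source, and 5.2(d) encourages prompt daily disclosure by field workers. DSMC meeting frequency and a reporting line to the DSMC are what the promised monitoring plan would normally contain, and that plan is not shown. Nor can the dry season be called low-risk: 5.1 says transmission is lower then, but section 4 says it is high throughout the year.

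**Conclusion.** Two points are established from the text alone. First, 5.5 and 5.9 specify a primary-outcome analysis and file, while 5.8(b) relies on outcomes that neither includes. Apart from parasite density, the specified package does not support the severity and complication grounds. Second, 8.5 as written makes onward reporting of a death or admission depend on one person's decision, with no stated path to the DSMC. A later monitoring plan may add detail, but it does not by itself remove a rule stated here.

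The missing wet-season review is a matter to confirm, not a demonstrated error. It deserves an answer because 5.1 itself says: "It is possible that during the dry season no impact of iron will be detected, while during the wet season, an impact will be observed". No estimate of deaths or admissions is part of this conclusion, since any such figure would rest on assumed rates.

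**What to change.** 1. **Reconcile 5.5, 5.8(b) and 5.9.** Define the Phase I DSMC dataset as the primary outcome plus deaths, hospital admissions, cerebral and severe malaria, pneumonia, diarrhea and dehydration, by arm, and use the same list in all three places. These events are already collected. The cost is wording plus more cleaning in the two-week May window; no children or procedures are added.
2. **Amend 8.5.** Remove the discretionary step for deaths, admissions and severe malaria, so that these go automatically to the PI, both IRBs and the DSMC. Discretion can stay for non-serious events. The cost is wording and some reporting work.
3. **Suggestion.** The sponsor should confirm that the detailed monitoring plan provides a DSMC safety review during the wet season. This has a practical limit. At the timetable's pace (2 weeks' cleaning plus 2 weeks' assessment), a review at the midpoint of the 22-week phase would report at week 11 + 4 = 15, with 7 weeks left, so a useful review needs a short list of serious events and a fast turnaround.
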